## Objectives

As a research project, our main objective is to develop a capacity-building strategy to obtain, improve, and retain skills and knowledge needed to develop and use “Living evidence synthesis” among members of health system organizations in charge of developing KT products to inform health decisions.

Specific objectives are:

- To design and evaluate a framework for the incorporation of living evidence synthesis in the development of three types of KT products to inform health decisions: recommendations in clinical practice guidelines [CPG], health technology assessment reports [HTA], and structured evidence summaries [SES] for institutional or public policies.

- To build capacity among members of health system organizations in the use of innovative and effective tools to support the generation and maintenance of living evidence synthesis.

- To develop living evidence synthesis for KT products to inform health decisions in a real setting

- To assess the effectiveness and usability of the Epistemonikos-L.OVE platform as a tool for keeping the living evidence process, as part of the development and updating of the different KT products

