### Data collection and analysis

Several measures will take place during the whole project in order to assess: the LE-implementation framework; the training workshops on Epistemonikos tools; and the capacity-building strategy used for participant health system organizations be able to implement the “living evidence” process in the development of KT products. All the participants will be invited to answer the questionnaires or the in-depth interviews to complete these assessments. The evaluations will be limited to what is necessary to meet the study objectives.
Figure 3 presents the timeframe and when evaluations will take place.

The expected size of the data collected for this assessment will be given by the number of participants who join the project from each organization.

**
*Evaluation 1. Assessment of training workshops*
**

After finishing each training session (workshop) participants will be asked to answer anonymous online surveys to assess the workshop’s materials (i.e. learning guide and objectives, support instructions and tutorials), training activities as well as the skills of the teacher who led the session and the presentation that he/she used to present the key concepts and procedures. The structured questionnaire will ask the participants to indicate his/her level of agreement (from strongly agree to strongly disagree), using a five-point Likert scale, with a series of statements that will allow us to evaluate the relevance and appropriateness of the aspects of the training workshop.

Data obtained from these surveys will be analyzed using summary measures (e.g. proportion of participants who answer each of the five Likert scale options). These data will allow researchers to redefine this part of the capacity-building strategy (if necessary). Training workshops can be also re-evaluated accordingly.

**
*Evaluation 2. Effectiveness and usability of the Epistemonikos tools and L.OVE platform*
**

All members of technical teams and task forces taking part in the study will be invited to respond to an online survey once the initial evidence synthesis process has been completed. The survey will be anonymous but will collect information about:

- Individuals' demographic characteristics and background (e.g. age, academic degree, amount of experience)

- Previous experience in developing evidence synthesis and/or systematic reviews

- Knowledge and previous experience planning and performing literature searches

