- Knowledge and previous experience completing the literature screening process

This survey will evaluate the usability and performance of the Epistemonikos L.OVE platform as a tool for evidence identification, screening and maintenance of the living evidence process. The information asked to assess performance will be limited to that directly related with the tasks participants must complete by using the Epistemonikos L.OVE tools, such as planning of evidence synthesis and evidence monitoring and surveillance (including screening, classification and study selection). The information asked to assess usability will be based and limited to participants experience using the tools for the tasks mentioned above. The survey will ask participants to indicate his/her level of agreement (from strongly agree to strongly disagree), using a five-point Likert scale, with a series of statements that will allow us to evaluate the usability and performance of the tools.

Data obtained from this survey will be analyzed using summary measures (e.g. proportion of participants who answer each of the five Likert scale options).

**
*Evaluation 3. Assessment of the capacity-building strategy*
**

To achieve this objective, two complementary approaches will be used for collecting data: an online survey to all the participants and in-depth interviews to a randomly selected number of participants. The online survey will be conducted at six months after the evidence surveillance period has started. All members involved in the evidence synthesis development from participant organizations will be invited to respond to the online survey. Data to be collected in this survey will be limited to that necessary for evaluating:

Clarity, relevance and timeliness of weekly messages sent to participants informing tasks and procedures.Clarity, completeness and utility of the Manual of Standardized Operating Procedures and its instructions.Clarity and timeliness of the support given by the expert researcher assigned to the group.Clarity and timeliness of solutions provided to doubts and difficulties that arises during the process.Satisfaction with results obtained (as individual and as member of the organization group) by developing the living evidence synthesis under the learning by doing methodology.

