### Expected results

This project will generate different types of results:

- An effective capacity-building strategy to implement the living evidence model in different KT products.

- The generation of living evidence synthesis for KT products directly applicable to the real-setting situations.

- A LE-implementation framework to incorporate living evidence in the KT products that can be applicable to any country or region.

- The integration of the Epistemonikos-L.OVE platform as a tool for keeping the living evidence process, as part of the development and updating of GPC, ETS, SES to inform health decisions.

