### Study status

Currently we have enrolled the organizations, and their participants have completed the training modules in LE synthesis and Epistemonikos L.OVE platform tools. Moreover, we have developed the first draft of the LE Implementation Framework that is ready to undergo the expert’s assessment for feedback.

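### The strategy is meant to build and retain skills and is expected to be 'effective', but none of the four evaluations measures participants' skill or knowledge as an outcome

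*Protocol article*

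**What the plan says.** All references are to the protocol article.

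- **Objectives.** The stated aim is: "our main objective is to develop a capacity-building strategy to obtain, improve, and retain skills and knowledge needed to develop and use". What is to be produced and used is living syntheses, and the people concerned are staff who prepare knowledge-transfer products.
- **Expected results.** The first item is: "An effective capacity-building strategy to implement the living evidence model in different KT products".
- **Evaluation 1 (workshops).** An anonymous agreement survey after each session covers the materials and slides shown, and also "training activities as well as the skills of the teacher who led the session". Its statements are ones "that will allow us to evaluate the relevance and appropriateness of the aspects of the training workshop".
- **Evaluation 2 (platform).** The stated purpose is: "This survey will evaluate the usability and performance of the Epistemonikos L.OVE platform as a tool for evidence identification". Study selection and upkeep of the evidence are covered too. It is anonymous and is given once, after the initial synthesis. It also asks for background, including self-reported knowledge and experience of searching and screening.
- **Evaluation 3 (the capacity-building strategy).** The survey comes six months into surveillance: "Data to be collected in this survey will be limited to that necessary for evaluating" a list of five topics. Four concern the clarity, timeliness, relevance, completeness or utility of messages, manual, expert support and answers to difficulties. The fifth is satisfaction with results. Interviews with a stratified random sample, at the end of follow-up, ask for perceptions of the strategy and the framework.
- **Evaluation 4 (framework).** Two questionnaires are planned. Technical staff report their experience of using the framework. Group leaders report on comprehension, usability and how developers are using its guidance and pathway.
- **Phase 3.** Each organisation's members are expected to produce at least one living synthesis, in a working group that includes a member of the research team.
- **Study status.** Organisations are enrolled and "their participants have completed the training modules in LE synthesis and Epistemonikos L.OVE platform tools".

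**The concern.** To improve and to retain are statements about change over time in a person's ability. Showing either needs some measure of that ability and at least two points to compare. The evaluation that carries the name of the capacity-building strategy asks instead about the quality of the support and about satisfaction.

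High satisfaction, a usable platform and a clear manual are all compatible with no change in what participants can do. If the study is run as written and then reports an effective strategy, no planned measure of skill stands behind that word. Because the results are meant to carry over to other countries and regions, the claim would travel well beyond these organisations.

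Timing adds to the problem: training is already complete, so a prospective pre-training baseline can no longer be taken.

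**Working it through.** The protocol article states no sample size calculation, error rate or target effect, so there is no figure to reproduce. The check sets each evaluation against the construct in the main objective.

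| Evaluation | What is measured | When | Participant skill or knowledge as an outcome? | Repeat measure of it? |
|---|---|---|---|---|
| 1 | Relevance and appropriateness of workshop, teacher, materials | After each session, anonymous | No | No |
| 2 | Usability and performance of the platform; background knowledge of searching and screening | Once, after the initial synthesis, anonymous | No (background only) | No |
| 3, survey | Support, manual, messages, satisfaction | Once, six months into surveillance | No | No |
| 3, interviews | Perception of strategy and framework | Once, end of follow-up, sample only | No | No |
| 4 | Experience with, comprehension of and use of the framework | Once, before the interviews | No | No |

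**Count.** Evaluations with a skill or knowledge outcome: 0 of 4. With a pre-training measurement: 0 of 4. With a repeat measurement that could show improvement or retention: 0 of 4. The only skills rated as such are the teacher's, in Evaluation 1.

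**Could existing items be linked to show change?** The Evaluation 2 background items come after training and after the first synthesis, are collected once and are anonymous. They have no earlier or later counterpart to be paired with.

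**Could the Phase 3 product stand in?** A completed living synthesis is a real behavioural result, but no evaluation counts or scores it. Because a research-team member sits in every working group, completion alone would not show that the organisation's own staff did the work.

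**What could a before/now rating deliver?** The recruitment aim gives a minimum of 3 types × 2 organisations × 3 members = 18 people in 6 organisations. The figures below are illustrative and in units of the SD of within-person change; the intraclass correlation (ICC) is an assumption.

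- Full response and independent participants: a two-sided 5% paired t-test at n = 18 has 80% power for 0.70 SD.
- Clustering, design effect 1 + (3 − 1) × ICC. ICC 0.1 gives 1.2, effective n = 18/1.2 = 15, detectable change 0.78 SD. ICC 0.2 gives 1.4, effective n = 18/1.4 ≈ 13, detectable change 0.85 SD.
- Only 12 independent responders: 0.89 SD.
- Half-width of a 95% confidence interval using 6 organisations (5 degrees of freedom, t = 2.571). ICC 0.1: 2.571 × √(1.2/18) = 0.66 SD. ICC 0.2: 2.571 × √(1.4/18) = 0.72 SD.

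At the planned minimum, only a rough estimate of self-perceived change is available. That is worth reporting with its interval, but does not justify a power claim.

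**The case against.** Five points can fairly be made for the plan.

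1. **The objective is to develop a strategy, and the assessments are partly formative.** The Design section says that their results will be used to redefine and improve the strategy and the framework. This stands, and it makes satisfaction and usability data legitimate. It does not stretch to calling the strategy effective.
2. **Some knowledge is recorded.** A reader might infer that the plan never touches participants' knowledge at any time. The documents do not support that, because Evaluation 2 asks about searching and screening knowledge. Those items are background, asked once and anonymously, so they cannot show change.
3. **Some behaviour is recorded.** A reader might also infer that the study could only say that participants liked the support. That goes too far as well. The leaders' questionnaire asks how developers use the framework and follow its pathway, and the interviews ask whether the framework guides usual work. These are single self-reports on framework use, not measures of skill.
4. **This is a condensed article.** The operations manual, the module guides and the training questionnaires are in a repository, and Figure 3 is not visible here. GRADE workshops are offered according to prior training, which suggests that some ascertainment took place. Individual items or baseline information may therefore exist unseen. But the article itself fixes what each evaluation covers and limits the six-month survey to its list, so the gap is stated and not merely left out.
5. **Retrospective self-ratings share the weakness.** Without a control group, rating oneself before and now is open to recall and self-report bias and is not a test of skill. This stands fully, and it limits what the fix may claim.

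**Conclusion.** The point holds in this form: the plan's four evaluations contain no outcome measure of participants' living-evidence skill or knowledge (0 of 4) and no repeated measure of it (0 of 4), and the expected syntheses are not used as an outcome. As written, the study can report acceptability, usability, perceived usefulness and self-reported framework use. It cannot show a gain in capacity or its retention, so it cannot support the word 'effective' in the sense of its own main objective.

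This rests on the content of each evaluation as the article describes it; questionnaires held in the repository were not available to check.

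A reader might think that adding self-ratings would supply a well-powered proof of effectiveness at the planned size. The documents do not support this. Eighteen is a recruitment aim, participants are clustered by organisation, and self-perceived change without a comparison group cannot carry that conclusion.

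**What to change.** 1. **Count what was done.** From project records, report out of all enrolled organisations how many completed at least one living synthesis and how many completed at least one surveillance and update cycle. For each, state whether the research-team member in the working group performed the step.
2. **Add a short before/now block to the six-month Evaluation 3 survey.** Participants rate their ability before the training and now on the main training objectives. Both ratings sit in one questionnaire, so they can be paired without identifying the respondent. If the survey is anonymous, record the organisation by a code so that clustering can be handled. Report the within-person change descriptively, with a 95% confidence interval that allows for clustering by organisation. Label it as self-perceived change, subject to recall and self-report bias, and make no power claim. Widen the closed list in the survey description to admit this block.
3. **Limit the conclusion.** Conclude that the strategy was acceptable, usable and perceived as useful, with the observed completion rates. Do not call it effective on satisfaction or uncontrolled self-ratings alone, and amend the first item of Expected results to match.

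The cost is a few more survey items, a tally from existing records and a more modest headline claim. An organisation code also narrows anonymity somewhat in groups of about three people, so responses should be reported only in aggregate.

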### Sampling

We will seek to involve three types of organizations from the health sector, that fulfill the characteristic of synthesizing evidence to develop KT products aimed at supporting health decision-making. 1) Health technology assessment [HTA] agencies; 2) secondary and tertiary healthcare institutions (hospitals) involved in institutional HTA programs and 3) clinical practice guideline [CPG] development organizations.

The identification of these organizations will be done through the networking relationships that the IIB Sant Pau has, where the Ibero-American Cochrane Center operates, which is recognized in Europe for its different developments in the area of evidence synthesis, and support for the evidence-based medicine. Its relations of interest for this project include: scientific societies and organizations of the Spanish Biomedical Research Network Consortiums (CIBER)
^
26
^, clinical guideline development organizations in Europe, and hospitals participating in a program that promotes evidence-based informed policies in healthcare institutions in Spain
^
27
^

The director or leader in charge of the evidence synthesis team from these organizations will be approached to present the project and invite them to take part. We will seek to enroll at least two organizations of each type described above, by a convenient sample.

Each enrolled organization will be asked to involve at least three members of their organization's technical team in charge of developing evidence synthesis to support decision-making. To take part in the study, the members of organizations should meet the following selection criteria:

- To be a contracted worker in the organization

- To be involved in evidence syntheses development tasks

- To complete and provide the informed consent for individual participation in the study

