At the end of follow-up (i.e. the end of the PICO question evidence monitoring) we will perform semi structured in-depth interviews to a randomly selected sample of participants. The randomization will be performed as a stratified random sample (including two groups/strata: a) technical team and/or taskforce members and b) team leaders), to guarantee that members from each group will be represented in the sample. This will be performed using Excel (version 16.34) software. These interviews seek to obtain information about participants´ perception of:

-The capacity-building strategy (i.e., training workshops, instructions and tutorials, accompaniment in “learning by doing” process, among other activities completed to refine the strategy within the study progress).-The LE-implementation framework and its effectiveness to guide the incorporation of living evidence synthesis processes into their usual working tasks (either for producing KT products or other evidence synthesis process to inform decision makers).

The interviews will be carried out by a third-party expert in this type of interview, with a script of questions generated by the research group. The data obtained from these interviews will be included anonymously in the Nvivo® (version 12)
^
32
^ program by the same third party and analyzed as qualitative data by an expert in the subject.

**
*Evaluation 4. Assessment of the LE-implementation Framework*
**

As presented before, the in-depth interviews will serve to evaluate the LE-implementation framework and its effectiveness in guiding the incorporation of living evidence synthesis processes into the participant’s usual working tasks in a sample of participants. To obtain information from all the participants, an online survey using Google Docs will be conducted prior to these interviews. Two types of questionnaires will be developed for this end, one for organizations technical team members and the other for organization’s group leader.

*-Technical teams' questionnaire:* This questionnaire will have a set of questions assessing participants experience with the use of the LE-implementation framework for planning and guide the living evidence synthesis.

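### The interview draw is stratified by role only, so an organisation type can by chance have no interviewee; adding type as a stratum is a minor, low-cost improvement

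*Protocol article*

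**What the plan says.** Data collection and analysis, Evaluation 3, plans "in-depth interviews to a randomly selected number of participants" at the end of follow-up. It then sets the method: "The randomization will be performed as a stratified random sample", with two strata defined by role ("including two groups/strata: a) technical team and/or taskforce members and b) team leaders"). The stated reason is "to guarantee that members from each group will be represented in the sample", where the groups are the two roles. No number of interviews is given, in total or per stratum.

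The Sampling section builds the study population differently: "We will seek to involve three types of organizations from the health sector" (HTA agencies, hospitals with institutional HTA programmes, and guideline developers). On numbers it says "We will seek to enroll at least two organizations of each type described above, by a convenient sample", and "Each enrolled organization will be asked to involve at least three members of their organization's technical team". The Design section organises the empirical work in three work packages that differ by target group or by the type of product made.

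The interviews cover the capacity-building strategy and also feed Evaluation 4, where "the in-depth interviews will serve to evaluate the LE-implementation framework and its effectiveness in guiding the incorporation of living evidence synthesis processes" into participants' usual work.

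**The concern.** The authors stratify because a simple random draw can miss a group that matters. They apply that protection to role and not to organisation type, although type is the axis on which organisations are recruited. With a small pool and a small number of interviews, random draws within role can leave one type with nobody.

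The interviews ask how the strategy and the framework worked within an organisation's usual tasks. If, say, no guideline developer is drawn, the study has no in-depth account of how the framework fitted that setting. The Expected results section looks for a strategy that works across different products, so the gap would fall on a question the study cares about.

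**Working it through.** The article gives no interview number and no probability, so there is no figure of its own to reproduce. The check is how likely the written scheme is to miss a type.

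**Inputs from the article (Sampling; Evaluation 3).** Three types; at least two organisations per type, so at least 3 × 2 = 6; at least three members each, so at least 6 × 3 = 18 participants; two strata, by role.

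**Assumptions.** One leader per organisation. Case A: the leader is one of the three members, giving 6 leaders and 12 technical members (2 and 4 per type). Case B: the leader is additional, giving 6 leaders and 18 technical members (2 and 6 per type). Case C: uneven enrolment of 2, 4 and 6 organisations per type, each with one leader and two technical members, giving 12 leaders and 24 technical members. Interview numbers are a range. Draws are independent between strata and without replacement, and everyone drawn takes part.

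**Formula.** For l leaders and k technical members in case A, inclusion–exclusion gives

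P(some type has no interviewee) = 3 × [C(4,l)/C(6,l)] × [C(8,k)/C(12,k)] − 3 × [C(2,l)/C(6,l)] × [C(4,k)/C(12,k)].

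**Numbers, case A**

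- 2 + 3: 3 × (6/15) × (56/220) − 3 × (1/15) × (4/220) = 0.3055 − 0.0036 = 0.302
- 3 + 3: 3 × (4/20) × (56/220) − 0 = 0.153
- 2 + 4: 3 × (6/15) × (70/495) − 3 × (1/15) × (1/495) = 0.1697 − 0.0004 = 0.169
- 3 + 4: 3 × (4/20) × (70/495) = 0.085
- 3 + 6: 3 × (4/20) × (28/924) = 0.018
- 4 + 8: 3 × (1/15) × (1/495) = 0.0004

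The same method with the other pools gives:

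| Leaders + technical | Total | A: 6 + 12 | B: 6 + 18 | C: uneven, 12 + 24 |
|---|---|---|---|---|
| 2 + 3 | 5 | 30.2% | 31.9% | not computed |
| 3 + 3 | 6 | 15.3% | 16.2% | 37.7% |
| 2 + 4 | 6 | 16.9% | 19.3% | 38.3% |
| 3 + 4 | 7 | 8.5% | 9.7% | not computed |
| 3 + 6 | 9 | 1.8% | 3.0% | 17.2% |
| 4 + 8 | 12 | 0.04% | 0.2% | 7.5% |

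A simulation of 200,000 draws for 2 + 4 in case A gave 0.1694 against 0.1693 exact.

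**Two related quantities, cases A and B for leaders, case A for organisations.** Drawing 3 of 6 leaders covers all three types in 2 × 2 × 2 = 8 of C(6,3) = 20 draws, so a type has no leader interviewed in 1 − 8/20 = 60%; with 2 leaders this is certain. At 3 + 3, the expected number of the six organisations without an interviewee is 6 × (1 − 3/6) × C(10,3)/C(12,3) = 6 × 0.5 × 120/220 = 1.64.

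**After the change.** With type as a stratum and at least one draw per type, the chance that a type is not drawn is 0. Refusals could still leave a gap.

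**The case against.** The strongest counter-argument is that the size is unknown. The enrolment figures are minimums, Study status says the organisations are already enrolled without giving counts, and the interview number is not stated. With balanced enrolment the risk is small at 9 interviews and negligible at 12. A reader might infer that the scheme will often miss a type; the article does not support that, because it holds only for few interviews or uneven enrolment. Nor is the missing number itself a fault: this is a condensed article, and Extended data lists a project operations manual that is not shown. What remains is the stated choice of strata.

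A reader might also infer that a missed type would be lost to the evaluation. It would not. Evaluations 3 and 4 survey all participants on the strategy and the framework, and group leaders have a separate questionnaire on using the framework in their organisation's current process. Those instruments are structured and summarised descriptively, so they do not replace an interview, but they do give evidence on every type that responds. Nothing in the article says that interview findings will be extended to a type that was not interviewed.

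Finally, type and product do not map one to one. Phase 3 lets organisations choose their product, and the first two work packages each span several kinds of organisation. Stratifying by type therefore need not balance product, and role is a sensible stratum because the Evaluation 4 questionnaires differ by role. This supports keeping role; it is not a reason to leave type unprotected.

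**Conclusion.** The point holds as a minor one. As written, the draw guarantees both roles and does not guarantee any organisation type. Under minimum, balanced enrolment (cases A and B) the chance of missing a type is about 30–32% at 5 interviews, 15–19% at 6, 8.5–10% at 7, 2–3% at 9 and near zero at 12. Under the assumed uneven enrolment it is still about 17% at 9 and 7.5% at 12, and a convenience sample with only a minimum per type allows such imbalance. These figures rest on assumed role counts, enrolment and interview numbers. What is at stake is the in-depth account from one type, alongside surveys that still reach everyone.

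**What to change.** In Evaluation 3, add organisation type as a stratum alongside role, and draw at least one interviewee per type; this needs at least three interviews. Where six or more are planned, draw at least one leader and one technical member per type (three of each), from different organisations where possible. Random selection within cells and representation of both roles are kept.

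Type is known from enrolment and the interviews come at the end of follow-up, so the change amounts to an extra column in the Excel sampling list. The cost is a slightly more constrained draw. The full type-by-role version needs at least six interviews, so a plan for five would have to add one or use the simpler version.
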